### OBJECTIVES:

The objective of this randomized controlled trial is to test the effect of screening patients in Penn Medicine Emergency Departments for eligibility of public benefits programs and using text messages post-discharge to connect patients to benefits enrollment specialists at Benefits Data Trust (BDT). Eligible patients will be randomly selected to receive text messages for two weeks after Emergency Department discharge with the phone number to speak with a benefits enrollment specialist at BDT. The number of calls to the BDT phone line and the number of submitted applications to public benefits programs will be compared between patients receiving a summary flyer with the phone number for BDT and the text message intervention to connect with BDT in comparison to an active control group who receives only a summary flyer with the phone number for BDT.

**Primary outcome variable(s):** Participant connection to BDT measured by phone calls completed by confirmed participants to BDT.

**Secondary outcome variable(s):** Number of applications for public benefits programs submitted per participant by BDT.

### BACKGROUND:

Every year, Philadelphians fail to claim approximately \$450 million dollars in federal and state benefits. Across the United States unclaimed benefits are estimated at approximately \$60 billion. These benefits include support for food, housing, healthcare, economic support, and others that can make a significant impact on well-being, upward mobility, and financial stability. The reasons that benefits are unclaimed are numerous, including lack of awareness about benefit programs and eligibility criteria, lack of agency and self-efficacy in completing expansive application requirements and organizing the necessary paperwork, and navigating the psychological costs of stigma associated with seeking public benefits. In accordance with incentive structures developed as a result of the Affordable Care Act, health care systems have demonstrated value in screening for patients' social needs and creating partnerships with public service agencies to connect patients to social services to improve individual and population health and reduce health care disparities. Patients presenting to emergency departments are more likely to possess unmet social needs. Thus, it is critical for health care providers in emergency departments to effectively identify patients' social needs and connect patients to social services agencies that can provide both immediate and long-term assistance through the connection to public benefits programs.

Benefits Data Trust (BDT), a benefits support organization based in Philadelphia, has a long track record of success in consistently securing benefits for individuals with unmet social needs. BDT assists individuals with the completion and submission of applications for 19 public benefits programs (e.g., Supplemental Nutrition Assistance Program, the Low-Income Home Energy Assistance Program, and the Pharmaceutical Contract for the Elderly) via different channels, including web, phone, text, and in-person support services. Trained outreach specialists are knowledgeable about the intricacies of benefits applications and eligibility requirements, and support is available in multiple languages. Building trust with clients and serving vulnerable underserved communities is a central focus for outreach specialists. For

services that they do not provide assistance for, BDT is also staffed to provide warm handoffs to help connect individuals to relevant organizations.

The focus of this proposal is to test whether patients identified in Penn Medicine Emergency Departments (ED) randomized to receive a warm handoff text messaging intervention are more likely to connect to study-specific BDT phone line and submit more applications for public benefits programs in comparison to patients who only receive a summary flyer with the BDT study-specific phone line upon discharge from the Emergency Department.

We propose to first survey patients to determine their eligibility for public benefits programs. Second, patients who are eligible for at least 1 of the 10 benefits programs to which BDT provides direct application support to complete applications will be randomly selected to either receive a flyer with the study-specific BDT phone number to apply for public benefits programs (active control) or receive a text messaging intervention for two weeks after leaving the ED with instructions to connect to the BDT study-specific phone line in addition to the flyer. Patients randomized to the intervention arm will receive an initial text message one day post-discharge from the ED with instructions for connecting with BDT and will receive subsequent reminders to connect with BDT on Days 3, 7, and 14 post-discharge. Patients who indicate that they have successfully connected with BDT on Day 3 will not receive intervention messages on Days 7 and 14. All patients, both those randomized to the control and intervention groups, will receive an end-of-study survey on Day 14 post-discharge from the ED to assess the patient's experience in the research study and provide a reminder about the number to connect with BDT.

Insights from this randomized controlled trial will inform future work evaluating benefits enrollment outcomes, the relationship between benefits enrollment and health care outcomes, and variations in health services use among patients connected to BDT in the ED.

## CHARACTERISTICS OF THE STUDY POPULATION:

VERSION 01-12-2024

### 1. Target Population and Accrual:

The target population of this study includes patients presenting in Penn Medicine Emergency Departments (ED).

Target sample size: 188 patients

Pilot study: 30 patients

RCT: 158 patients

Power calculations were based on preliminary testing and a prior assumptions that a baseline rate of about 1% of patients would contact BDT after receiving a flyer at the time of discharge (control group), and 10% of patients would contact BDT after receiving text messages (intervention group). Based on these parameters, we estimate that a sample of 158 patients (79 per arm) would provide at least 80% power to detect a 9% difference between the two study arms, with one-sided statistical testing.

For practical reasons related to study funding and allocation of research staff, we may include one pre-specified interim analysis.

Alpha spending function using O'Brien Fleming efficacy boundary

For  $k = 2$

|     |        |        |
|-----|--------|--------|
| $P$ | 0.0088 | 0.0467 |
|-----|--------|--------|

|     |    |     |
|-----|----|-----|
| $N$ | 80 | 160 |
|-----|----|-----|

### 2. Key Inclusion Criteria:

Patients will be included in the study based on the following criteria:

- Adults at least 18 years of age
- Patients must legally reside in the city of Philadelphia
- Patients receiving care from Penn Medicine Emergency Departments at the Hospital of the University of Pennsylvania and Penn Presbyterian Medical Center who are deemed unlikely to require inpatient hospitalization or observation at the time of enrollment
- Patients must have one of the following insurance plans: Medicaid and/or Medicare (managed and traditional).
- Patient must be able to read/write in English.
- Patients must be eligible for at least 1 of 10 the benefits programs for which BDT can provide either direct application assistance or provide referral to the social services agency website to submit applications.

### 3. Key Exclusion Criteria:

Patients will be excluded from participating in the study based on the following criteria:

- Individuals < 18 years
- Does not speak/read English
- Unable to consent or communicate
  - Patients deemed by ED physicians to be in critical or unstable condition
  - Patient is in severe distress, e.g., respiratory, physical, or emotional distress
  - Patient is intoxicated, unconscious, or unable to appropriately respond to questions
- Patients under police custody
- Patients without a stable mobile phone number for the next 21 days

#### **4. Subject Recruitment and Screening:**

Patients will be recruited in Penn Medicine Emergency Departments (EDs) at the Hospital of the University of Pennsylvania and Penn Presbyterian Medical Center by trained clinical research assistants. Clinical research assistants will pre-screen patients in the ED via the Electronic Health Record (EHR) to determine whom to approach. Patients will be considered appropriate to approach if they meet the inclusion and exclusion criteria specified above and are determined to be likely discharged from the ED. Patients potential to be triaged to be discharged from the ED will be identified using the following recruitment guidelines: 1) First, patients should have a low acuity level as indicated by the Emergency Severity Index (ESI) level in the EHR. Acuity levels range from Level 1 (highest acuity) to Level 5 (lowest acuity). Patients at levels 3-5 will be prioritized. 2) Clinical research staff will then approach clinician staff in charge of patient care (e.g., physicians or nurses) to confirm the probability of the patient's discharge from the ED.

Eligible patients will be approached in the ED, provided with a brief introduction to the study, and asked if they are interested in participating. Interested participants will complete a brief eligibility survey that confirms the final inclusion and exclusion criteria for eligibility. Participants who are deemed initially eligible will then provide written electronic informed consent in REDCap followed by the Benefits Launch Express (BLX) survey. The BLX survey is a web-based survey managed by BDT which provides initial information about a participant's potential eligibility for at least one of the benefits programs for which BDT provides direct application support or referral. Completion of the BLX survey is necessary to confirm final eligibility for the study. Results of the BLX survey will be manually transferred from the BLX webpage back into the REDCap eligibility survey. After completion of the BLX survey, eligible and interested participants will create an account in the Way To Health platform, a brief baseline survey, and then proceed to be randomized. All communications with the patients will express that participation is completely voluntary and that they will be free to stop participating at any time.

We will use the Academic Associate (AA) Program at the Emergency Departments (ED) at the Hospital of the University of Pennsylvania and Penn Presbyterian Medical Center to assist with identifying patients. The AA Program provides pre-medical and pre-health post-baccalaureate students an opportunity to engage in clinical and translational research activities. The AAs have Immunization records (measles, mumps and rubella [MMR] and varicella [chickenpox]) and TB screening (PPD test or equivalent), and influenza (in season) and complete a web-based course sponsored by the University of Pennsylvania on the protection of human subjects in research. Using Epic tools, AAs, and trained clinical research coordinators, we will screen patients ages 18 and older who have Medicaid, Medicare, or no health insurance, are able to read/write in English, and reside within a Philadelphia zip code. Patients will be excluded from participating in the research study if they are less than 18 years, deemed to be in critical condition by ED physicians, do not read/write in English, present in severe distress (e.g., respiratory, physical, or emotional), are under police custody, have primary commercial/private health insurance benefits, or do not have a stable mobile phone number for the next 21 days.

#### **5. Early Withdrawal of Subjects:**

Participation in this study involves the completion of a brief screening survey and a baseline survey that includes the BDT Benefits Launch Express (BLX) benefits eligibility survey prior to randomization. Participants who are not eligible for at least one of the benefits for which BDT provides application support will not be randomized to continue in the study but will receive compensation for the time spent completing the pre-randomization survey. Participants randomized to the intervention arm will receive an initial text message one-day post-discharge with instructions for connecting with BDT and a follow-up text message two days later on Day 3 to assess connection success. Participants will then receive subsequent reminders to connect with BDT on Days 7 and 14 post-discharge. The message schedule will be adjusted to ensure that text messages are received during weekday business hours, with 1-2 day shifts depending on the weekday of enrollment. Participants who indicate that they have successfully connected with BDT will not receive subsequent messages. Text messages to patients will leverage insights from behavioral economics to improve the response rate to call BDT (see attached message scripts).

All participants, both those randomized to the control and intervention groups, will receive a final study survey on Day 14 post-discharge to assess the participant's experiences in the research study as well as the contact phone number to reach the BDT enrollment counselors. All participants will be informed that they may withdraw consent and leave the study at any time for any reason. Participants will be informed that they may opt out of receiving study text messages at any time by texting the word 'BYE.' Participants will also be informed that they will still receive a final text message 14 days after discharge from the emergency department inviting them to complete the final online survey.

## 6. Vulnerable Populations:

N/A

## 7. Populations vulnerable to undue influence or coercion:

N/A

## STUDY DESIGN:

We conducted a pilot study with 30 patients prior to launching the RCT in July 2023. The pilot study only enrolled participants to receive the intervention messages to test the design efficacy and implementation success of the text messaging system. We will now concurrently launch a two-arm prospective intervention randomized controlled trial that is expected to occur over 6 months in Penn Medicine Emergency Departments. The study will be conducted using Way to Health, a research information technology platform at the University of Pennsylvania used previously in digital health engagement clinical trials.

[figure not shown]

**Figure 1. Participant Flowchart**

The study team consisting of trained clinical research coordinators and Academic Associates, post-baccalaureate pre-health students employed in the ED to assist in clinical research activities, will recruit patients who are at least 18 years old who have Medicaid and/or Medicare health insurance, are able to read/write in English, and reside within a Philadelphia zip code. Patients will be excluded from participating in the research study if they are less than 18 years, deemed to be in critical condition by ED physicians and unlikely to be discharged, do not read/write in English, present in severe distress (e.g., respiratory, physical, or emotional), are under police custody, have primary private health insurance benefits or are designated self-pay or without health insurance, or do not have a stable mobile phone number for the next 21 days. Research staff will then approach patients and obtain informed consent using REDCap to confirm eligibility. The eligibility survey includes the BLX survey administered via secure website. In addition to meeting the study's inclusion/exclusion criteria, participants must also be eligible for at least one benefit for which BDT provides application assistance in order to be enrolled in the study and randomized. All participants will receive \$20 for completing informed consent and the BLX survey. Eligible patients will then create an account through the study website on Way To Health, complete a brief baseline survey, and will then be randomized to either the intervention or control arms.

## **Active Control Arm**

Participants in the control group will receive a summary flyer providing contact information for BDT, including the unique study phone line to connect with a BDT enrollment navigator. Currently, the standard of care is for ED patients to receive no information about public benefits. Therefore, the flyer represents an augmentation of usual care for patients randomized to the control group. Participants will also receive a one-time text message introduction to the study 2 hours after enrollment with a reminder that the study team will contact them in 14 days to complete a brief follow-up survey.

## **Intervention Arm**

Participants in the intervention arm will be instructed that study personnel will be contacting them the first day after discharge to help connect them to a BDT enrollment navigator to help them submit their applications for public benefits. At Day 1 post-discharge, participants in the intervention group will receive a text message to prompt them to call the BDT enrollment navigators to complete their applications for public benefits they screened for while in the ED. On Day 3, patients will receive a follow-up message to assess whether they have reached out to BDT. Those participants who indicate they have not yet connected with BDT on Day 3 will receive reminder text messages at Day 7 and 14 post-discharge.

## **METHODS:**

### **1. Study Instruments**

Participants will complete three surveys as part of their study enrollment. The Eligibility Survey completed in REDCap, a HIPAA compliant platform, will confirm that participants meet the defined inclusion/exclusion criteria. The BLX survey, which is administered via a secure website, assesses participant's potential eligibility for public benefits and will be used to confirm participant eligibility in the study. Participants must be potentially eligible for at least one of the benefits programs for which BDT provides direct application or referral support. Results from the BLX survey will be manually entered into REDCap by trained clinical research personnel. Eligible patients will then create an account in Way To Health, a HIPAA compliant online research platform used for many clinical research studies across Penn Medicine entities, and complete a baseline survey collecting data related to participant sociodemographic characteristics, attitudes towards application for public benefits programs, and health-related social needs.

After 14 days, the follow-up survey will be administered in Way To Health. Participants in the control group will also receive a BDT Summary Flyer detailing the ways in which they may contact a BDT enrollment counselor to complete the benefits application process.

The Informed Consent, Eligibility Survey, and BLX Survey will be completed on REDCap. Participants will complete the Baseline survey and End of Study survey on the Way To Health platform. A demo version of the BLX survey can also be reviewed at <https://uphs-staging.benefitslaunch.org/>.

### **2. Group Modifications:**

N/A

### **3. Method for Assigning Subjects to Groups:**

Study participants will be randomized following informed consent, confirmation of eligibility, and completion of the baseline survey. Participants will be randomly assigned to either the control or intervention groups. Participants will be randomized in block sizes of 6 via Way To health.

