All survey data will be stored in a secure, web-based database (Way to Health or REDCap) where a study ID number will be generated for each patient. A link between the study ID number and the patient PHI will need to be maintained to ensure that the study staff can track recruitment efforts to potential participants and to avoid contacting any patients who have previously declined to participate. To ensure that confidentiality is preserved, individual identifiers (such as name) are stored in a single password protected system that is accessible to study research, analysis and IT staff only. This system is hosted on site at UPenn and is protected by a secure firewall. Once a participant is in this system, they will be given a unique study ID number. Any datasets and computer files that leave the firewall will be stripped of all identifiers besides the study ID and individuals will be referred to by their study ID only, except when this information is required to share with Benefits Data Trust for collection of study outcomes (see below). The study ID will also be used on all analytical files. Way to Health and REDCap are secure web applications for building and managing online surveys and databases. Privacy of all study data will be maintained by restricting access to the identifiable information only to approved study staff who have received subject confidentiality and privacy training. Study coordinators will access patient contact information from the database to conduct recruitment phone calls. The study coordinator will review the consent script, which will include a description of the voluntary nature of participation, the study procedures, risks and potential benefits in detail. Participants will be told that all information will be kept strictly confidential, except as required by law. Subjects will be provided a copy of the consent document. All efforts will be made by study staff to ensure subject privacy. Enrollment will be conducted by the study coordinators who will enter patient information directly into the Way To Health platform once a participant has consented to participate. This database is hosted on a secure server as detailed in the subject confidentiality section. Study coordinators may have to contact patients in the intervention and their support partners during the course of the study and will use the WTH database to access contact information to facilitate this contact.

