## **INFORMED CONSENT:**

### **1. Consent Process:**

Informed consent will be obtained from all participants at the beginning of their study participation prior to completing the eligibility survey. Upon recruitment, individuals who are interested in learning more about the study will review the study information including its objectives, duration, and requirements with research personnel. The informed consent will detail the voluntary nature of the study, the risks and benefits of participation, alternatives to participation, and that participants can withdraw from the study at any time. Participants will be asked to sign the informed consent document to agree to participate in the study. Participants will be provided with details regarding how to contact the research team via email or phone at any time if they subsequently wish to withdraw from the study.

Participants will be given contact information (including telephone and email) for the principal investigator ([name]), and the University of Pennsylvania IRB to address any potential concerns. A detailed Manual of Operations will be developed for the study and procedures will be designed to ensure efficient and prompt updating. All study participants read and review the informed consent document with assistance from in-person research assistants. All study staff will undergo a thorough training and certification procedure prior to protocol implementation, including CITI Course in the Protection of Human Research

634 Participants online training in research ethics. The initial training will be conducted by the PI and will  
635 include an overview of the study, detailed explanation of the study protocol, and hands-on practice of  
636 specific protocol components. All study staff will be observed conducting randomly selected protocol  
637 duties at least twice annually and evaluated using specifically designed checklists.

638 2. ***Waiver of Informed Consent:***

639  
640 N/A

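### A single fixed block size of 6, in a trial with no masking described, leaves up to a quarter of assignments open to deduction; varying the block size would remove most of that risk at almost no cost

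*Protocol*

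**What the plan says.** Allocation is described in three sentences under Methods, Method for Assigning Subjects to Groups. On timing: "Study participants will be randomized following informed consent, confirmation of eligibility, and completion of the baseline survey". On arms: "Participants will be randomly assigned to either the control or intervention groups". On the mechanism: "Participants will be randomized in block sizes of 6 via Way To health". Six is the only size given. The section mentions no random variation, no strata or per-site lists, and no withholding of the block size from recruiters. The ratio is 1:1, since Target Population and Accrual says that "a sample of 158 patients (79 per arm) would provide at least 80% power", so each block is 3 + 3.

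Four other places bear on whether assignments can be anticipated:

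- **Arm visible after assignment.** The Intervention Arm section says "Participants in the intervention arm will be instructed that study personnel will be contacting them the first day after discharge". The protocol describes no masking of participants or staff. That the trial is unmasked is therefore an inference from its procedures; the protocol does not use the term.
- **Enrolment and follow-up contact.** Under Subject Privacy, coordinators enter consenting patients into Way To Health, and "Study coordinators may have to contact patients in the intervention and their support partners during the course of the study".
- **Training.** Under Consent Process, staff training will "include an overview of the study, detailed explanation of the study protocol, and hands-on practice of" specific components of it. The block size is part of that protocol.
- **Discretion before approach.** Under Subject Recruitment and Screening, research assistants pre-screen the health record to choose whom to approach and give priority to lower-acuity patients. "Clinical research staff will then approach clinician staff in charge of patient care" to confirm that discharge is likely.

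**The concern.** In a fixed 3 + 3 block, once three assignments to one arm have been made, the rest of the block is known. The last place is always known. If recruiters know the block size and can see or reconstruct past assignments, they can sometimes tell which arm comes next before the next patient enters. They could then, knowingly or not, favour an apparently interested patient when a text-message slot is due and pass over that patient when a flyer slot is due. The arms would then differ in motivation to call, which is close to the primary outcome. Adjusting for measured baseline characteristics would not fully correct this.

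The stakes are higher than usual because the trial turns on few events: about 1 caller in the control arm and 8 in the intervention arm.

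**Working it through.** **Inputs.** Block size 6 (Method for Assigning Subjects to Groups). 1:1 ratio, 79 per arm, control rate 1%, intervention rate 10%, one-sided test (Target Population and Accrual). Two-sample z-test for proportions at 0.05 (Statistical Analysis Plan, Detailed Description).

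**The plan's own figure.** n per arm = [z_α √(2p̄q̄) + z_β √(p₁q₁ + p₂q₂)]² / (p₂ − p₁)², with p̄ = 0.055:

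[1.645 × √0.10395 + 0.842 × √0.0999]² / 0.09² = 0.634 / 0.0081 = 78.3, rounded up to 79.

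The total is 158, and power at 79 per arm is 80.3%. The stated sample size is reproduced and is not in question.

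**Assignments known with certainty.** A 3 + 3 block has C(6,3) = 20 equally likely sequences.

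| Final places already determined | Sequences |
|---|---|
| 1 | 12 |
| 2 | 6 |
| 3 | 2 |

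Mean = (12×1 + 6×2 + 2×3)/20 = 30/20 = 1.5 of 6, or 25%. With 158 patients there are 26 full blocks and 2 patients over. That gives 26 × 1.5 = 39 certain assignments, and 39/158 = 24.7%.

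**Best guess.** Guessing whichever arm has more places left is right on average for 3 + (2⁶/20 − 1)/2 = 4.1 of 6 assignments, or 68.3%, against 50% by chance.

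**One list shared by two sites.** Suppose an observer sees a random half of the assignments but knows the block boundaries. To be certain, that observer must have seen all three assignments to the used-up arm, which has probability (1/2)³ = 1/8. The certain share is 25%/8 = 3.1% (3.2% by simulation).

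**Varied block sizes.** This simulation has 158 assignments and an observer who sees everything and knows the set of sizes but not their order.

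| Scheme | Certain | Best guess correct |
|---|---|---|
| Fixed 6 | 24.7% | 68% |
| Random 4, 6 | 5.5% | 69% |
| Random 4, 6, 8 | 2.2% | 68% |

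**Sensitivity of the result.** Pooled z = (x₁ − x₀)/79 ÷ √(p̄q̄ × 2/79), where p̄ = (x₁ + x₀)/158. The one-sided critical value is 1.645 (1.678 at the 0.0467 shown for the final look).

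| Callers, text v flyer | z |
|---|---|
| 8 v 1 (as planned) | 2.40 |
| 6 v 1 (two text callers lost) | 1.93 |
| 7 v 2 (one caller moved across) | 1.72 |
| 6 v 3 (two callers moved across) | 1.03 |
| 3 v 0 | 1.75 |
| 2 v 0 | 1.42 |

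**Effect of steering when the texts do nothing.** About half of the 39 certain slots, say 20, are text slots. Assume a 1% calling rate in both arms and fill all 20 slots with patients twice as likely to call. This adds 20 × 0.01 = 0.2 expected callers. By exact binomial enumeration, the chance of rejection rises from 2.1% to 3.6%, or to 5.5% if those patients are three times as likely to call. If the common rate were 2% (an assumption; the protocol plans on 1% for flyers), doubling would move it from 5.0% to 8.1%.

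**The case against.** The strongest reply is that the observer behind the 25% may not exist. Nothing in the protocol says that recruiters or coordinators can see a running allocation sequence in Way To Health, and enrolment is spread over several kinds of staff at two departments. This stands: 25% is an upper bound, and under a shared list that is only half seen the figure is nearer 3%.

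Second, approach and assignment are separated. After approach come the eligibility questions, consent, the benefits screening survey, account creation and the baseline survey. Patients who screen ineligible are never randomised, and on a shared list the other department may take the slot first. This also stands. The 25% counts successive randomisations, not approaches.

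Third, pre-approach screening uses record criteria, acuity and likely discharge, none of which measures willingness to call. This stands in part, because staff still meet the patient and administer the surveys before randomisation.

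A reader might infer that one steered patient could decide the trial, because 3 versus 0 callers is significant and 2 versus 0 is not. The planned figures do not support that. Those two outcomes together have a probability of about 1.6% under the planned rates, and from 8 versus 1 the result survives moving one caller. A steered patient is also not necessarily a caller.

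Finally, assignment by a platform after consent and baseline is a common arrangement, and the outcome comes from the benefits organisation's call records rather than from staff judgement. Both are true. Neither prevents someone from deducing the end of a fixed block, and objective records do not protect against a biased choice of who enters which arm.

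**Conclusion.** The point holds as an avoidable weakness. The protocol fixes one block size in a document on which recruiters are trained, in a trial whose procedures reveal the arm. The share of assignments that could be known in advance is at most 25%. It is about 3% for someone who sees a random half of a shared list and knows the block boundaries, and lower still if the sequence is hidden. The protocol does not give the list structure or the staff's view of the sequence, so the figure cannot be narrowed further.

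A reader might also infer that a quarter of assignments are in fact known, or that steering has occurred. The documents support neither. Under the planned 1% calling rate, even complete use of the certain slots has a modest effect on false-positive risk, though the effect grows if the underlying rate is higher. The sample size is unaffected. This is a low-priority improvement.

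**What to change.** For assignments still to be made:

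1. Configure Way To Health to draw block sizes at random, for example from 4, 6 and 8.
2. Replace the sentence giving the size with one saying that permuted blocks of varying size are used, and hold the sizes in a document that recruiters do not use.
3. Restrict recruiters' view of the running sequence, and state whether the two departments share one list or have separate lists.

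Step 1 lowers certain knowledge from at most 25% to about 2%. It does not lower the best-guess rate, which stays near 68% for anyone who still sees the sequence, so step 3 is needed to address guessing.

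The cost is a platform setting and a short protocol edit. The largest possible imbalance per list rises from 3 patients (half of 6) to 4 (half of 8). The Interim Analysis section reports an interim look, planned at about 50% enrolment, in the past tense. Some assignments have therefore probably been made already, and the change cannot reach those.
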